## Methods

### Study design

We will implement a stepped-wedge cluster-randomised controlled trial in 16 MAR communities. MAR system is a community-based intervention designed to supply low-salinity water for 60–70 households in a village or community. MAR intervention cannot be implemented and randomised at individual or household levels. Once a community will have access to MAR water, it is difficult to withhold the access of MAR water for some households. Therefore, we will conduct a cluster-randomised trial where each community will be considered as a cluster. The stepped-wedge design allows communities to gradually have access to MAR water; however, the point at which their access commences will be randomly assigned.^52^ In this way, each MAR site will contribute data for both the intervention and the control time periods. We will have five monthly steps in the stepped-wedge trial (figure 3). In the first step, none of the communities will have MAR water available for drinking and we will collect baseline information. During each subsequent month, four randomly selected communities will receive access to MAR water for drinking and cooking. In the last (fifth) monthly step, all the communities will have access to MAR drinking water.

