### Randomisation and intervention delivery

We will randomly select four MAR communities to drink MAR water in each step following the first (baseline) step (figure 3) by computer-generated random numbers. Randomisation will be conducted by an investigator who will not be directly involved in implementation of the stepped-wedge study and this will be done before commencement of the study. The study could not be blinded, therefore there was no concealment from the cluster participants. Although infiltration of rainwater and pond water into the brackish aquifer through the MAR systems will be ongoing for 1–2 years in each community, people will not have access to MAR water until a formal handover of MAR systems to community members. The implementers hire a caretaker or gatekeeper for each MAR community who is responsible for maintenance of the respective MAR system prior to the community handover. The implementers form a community management team who are responsible for maintenance of each MAR system following handover. We have synchronised the community handover with the randomisation schedule in the 16 communities after consulting with the gatekeepers. Community health promoters will inform the participants when the MAR water will be available for consumption once the community management team is formed. Agreement of the implementers and gatekeepers was sought at the beginning of the study during site selection for inclusion of any site in trial and access of MAR water as per the randomisation.

We will deploy a local trained promoter at each MAR site, who will visit these households, list members and identify pregnant women in these and other households in catchment areas of each MAR site. Promoters will encourage all household members to drink MAR water exclusively while they are at home, carry a bottle of MAR water while they go out for work and other activities, and to cook with MAR water. The community health promoters will visit households with promotional materials (eg, flip charts) from the beginning of the study to inform household members about adverse health effects of drinking brackish water and potential benefits of drinking low-salinity MAR water. As per the randomisation schedule, they will inform households when MAR water will be available for consumption.

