
### Data collection methods

The outcomes of interest will be measured from selected participants of 16 communities irrespective of their access to MAR water during five monthly visits. The interval between two successive blood pressure measurements or two consecutive data collection visits will be at least 4 weeks for each participant. After taking informed written consent from household heads and each participant, research staff will administer a survey using a structured questionnaire to collect information on drinking water sources, household members’ sociodemographic status, medical history, family history of cardiovascular diseases, medication intake, and cardiovascular risk factors including smoking history and alcohol intake during the first monthly visit. Exposure and outcome data will be collected in all five visits. Participants’ weight and hip circumference will be measured in all visits but height will be measured in one visit.

As part of the MAR uptake evaluation, the research staff will collect self-reported data on MAR water use from each household and whether households exclusively or intermittently use MAR water for drinking and cooking during follow-up visits. Research staff will also collect stored drinking and cooking water samples for measurement of electrical conductivity and will ask respondents the source of stored water.

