### Statistical methods

We will conduct an intention-to-treat analysis for the primary analysis. For the primary analysis, we will assess whether access to MAR water reduces the systolic blood pressure (continuous outcome) of the ≥20-year-old participants. Pregnant women will be included in the primary analysis because it is likely few pregnant women will be identified in the 16 communities and separate analysis of pregnant women will be underpowered. We will use generalised linear mixed models with appropriate links for the primary analysis considering random effects for community, households and participants, and fixed effects of steps or visits. We will adjust the effect of MAR systems on blood pressure for age, sex, weight and height, and personal and socioeconomic factors (table 2). We will inspect the missing data patterns and use multiple imputation with chained equations to jointly impute data on missing exposure and confounders to preserve an unbiased association estimate if the data are missing at random conditional on measured variables. We will also conduct subgroup analyses among the households that adhere with the MAR intervention and that exclusively use MAR water. If the trial demonstrates drinking MAR water has health effects, we will investigate the time required for health effects following receiving MAR intervention in secondary analysis.

**Table 2 T2:** Key variables to be used for assessing the health impact of access to MAR water

Outcomes	Exposures	Confounders	Covariates	Moderators
Systolic blood pressure	Access to MAR water	Sex	Age	Drinking/cooking from another water sources
Diastolic blood pressure	Drinking water salinity	Socioeconomic status	Weight	
Pulse pressure	Cooking water salinity	Education	Height	
Mean arterial pressure	Drinking water sources Cooking water sources		Waist circumference	
Urinary total protein Urinary sodium excretion			Mid-upper arm circumference	
			Adding table salt	
			Adding salt for cooking	
			Exercise level	
			Smoking status	
			Use of betel nuts	
			Stress	
			Diet	
			Urinary creatinine	

MAR, managed aquifer recharge.

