The study has several limitations. We will be unable to control salinity level of drinking water across the 16 MAR communities due to different hydrogeological conditions and volume of infiltrated water across the aquifers. Although the initial electrical conductivity of MAR water will be <2000 μS/cm, electrical conductivity is likely to vary across different MAR communities with the intensification of dry season. Therefore, MAR water salinity will differ across communities at a single point of time, and also for the same community at different points of time. This will result in different versions of exposures (ie, access to MAR water with different salinity levels) that may affect different responses for some participants depending on the version of exposure they will receive.^92 93^ To account this, we will specify the versions of exposure by measuring the salinity level of MAR water available in participants’ households and interpret the response as unit change of salinity at different MAR water salinity levels. As compliance of drinking MAR water may be different across communities despite active encouragement by promoters, one problem of the intention-to-treat analysis is that if the proportions of participants who will always drink MAR water are low compared with those who will not, the potentially greater effect of MAR intervention on blood pressure of fully participating individuals may be washed out by the smaller effect of those who will not comply. To account for this, as a secondary analysis, we will conduct ‘instrumental variable’ (IV) analyses by jointly running two regression models: a regression model for predicting urinary sodium excretion by drinking water salinity, and a regression model for blood pressure prediction given the urinary sodium excretion. The assumption of IV analyses is fulfilled in our context as the exogenous variable (IV) can only affect outcome variable (blood pressure) through influencing the endogenous variable (urinary sodium excretion).^94^ If MAR water has lower salinity than other water sources and if participants always drink MAR water, their urinary sodium excretion will be low compared with those who will not fully participate.

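### The analysis restricted to adhering, exclusive users of MAR water selects on behaviour after randomisation, may be biased, and is not repaired by the planned instrumental-variable analysis

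*Protocol article*

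**What the plan says.** All references are to the protocol article.

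- **Primary analysis** (Statistical methods): "We will conduct an intention-to-treat analysis for the primary analysis". The model is a mixed model "considering random effects for community, households and participants, and fixed effects of steps or visits".
- **Analysis in question** (same section): "We will also conduct subgroup analyses among the households that adhere with the MAR intervention and that exclusively use MAR water". The article does not say how adherence is judged, over which visits, or what the adherers are compared with.
- **How use is recorded** (Data collection methods): households report "whether households exclusively or intermittently use MAR water for drinking and cooking during follow-up visits". Staff also sample stored water and measure its salinity and conductivity (Exposure assessment).
- **Timing** (Randomisation and intervention delivery): of randomisation, "this will be done before commencement of the study". Nobody has access before formal handover. On blinding: "The study could not be blinded, therefore there was no concealment from the cluster participants".
- **Schedule** (Study design): "During each subsequent month, four randomly selected communities will receive access to MAR water for drinking and cooking".
- **Expected compliance** (Discussion): "compliance of drinking MAR water may be different across communities despite active encouragement by promoters". The strengths and limitations list adds that it may vary with socioeconomic status, which Table 2 names as a confounder.
- **Planned instrumental-variable (IV) analysis** (Discussion): a secondary analysis meant to deal with dilution by non-compliance. One regression predicts urinary sodium from drinking-water salinity; the other predicts blood pressure from urinary sodium.

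**The concern.** Randomisation fixes when a community gets access. It does not fix which households then use the water exclusively. Restricting to those households replaces a randomised set with a self-selected one, and the authors themselves expect the selection to be non-random. The Discussion rejects non-randomised designs because participation by residents with different characteristics would unbalance confounders. The adherer subgroup partly brings that difficulty back, and the article attaches no caveat to it.

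The Discussion foresees that low compliance could dilute the intention-to-treat effect. If that happens, an estimate in actual users becomes attractive as evidence on whether the water works, and the findings go to government partners. The estimate most exposed to selection could then carry the interpretation.

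**Working it through.** **1. Benchmark.** The plan's effect size is 3 mm Hg with SD 20. Its unadjusted sample size reproduces: 2 × (1.960 + 0.842)² × 20² / 3² = 697.7, so 698 per group and 1396 in total. No figure in the plan is disputed; 3 mm Hg is only the yardstick for bias.

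**2. Is the subgroup defined after randomisation?** Yes. Allocation precedes the study, access is impossible before handover, and use is recorded at follow-up visits. Stated willingness at enrolment does not fix later behaviour.

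**3. Does selection differ by sequence?** With a baseline visit and four monthly crossovers, the sequences have 4, 3, 2 and 1 post-access visits. If an adherer must report exclusive use at all m of them, with probability q per visit and visits independent, the share kept is q^m:

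| q (assumed) | Seq. 1 (m=4) | Seq. 2 (m=3) | Seq. 3 (m=2) | Seq. 4 (m=1) |
|---|---|---|---|---|
| 0.9 | 66% | 73% | 81% | 90% |
| 0.8 | 41% | 51% | 64% | 80% |
| 0.7 | 24% | 34% | 49% | 70% |
| 0.6 | 13% | 22% | 36% | 60% |
| 0.6, within-household correlation 0.3 | 28% | 34% | 43% | 60% |

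The last row uses a beta-distributed propensity with a = 1.4 and b = 0.933: E[q] = 0.6, E[q²] = 0.6 × 2.4/3.333 = 0.432, E[q³] = 0.432 × 3.4/4.333 = 0.339, E[q⁴] = 0.339 × 4.4/5.333 = 0.280. Perfectly persistent adherence, or a rule applied visit by visit, gives no such gradient in the households selected.

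**4. Does this bias the effect?** Illustrative simulation: 16 communities × 28 households × 5 visits, one blood pressure value per household-visit, true effect 0 or 3 mm Hg. The fitted model had community and household random intercepts and visit effects. Log-odds of adherence were 1.4 + 0.8 × a stable household trait. The Monte Carlo standard error was about 0.05. Negative values exaggerate the reduction.

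| Adherence related to | Bias, mm Hg |
|---|---|
| nothing | about 0 |
| a stable trait that shifts blood pressure level | −0.05 to −0.17 |
| a trait-related blood pressure trend | about 0 to −0.18 |
| blood pressure deviation at the same visit | −1.1 to −1.3 |

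The share kept under the all-visits rule ran from about 41% in sequence 1 to 77% in sequence 4 even in the first row. Unequal retention alone therefore did not bias the estimate. A model with community effects but no household effects was off by up to −1.0 in the stable-trait case, when adherers' post-access data were set against all control data.

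**5. Check on the last row.** If the log-odds of adherence fall by b per mm Hg and the visit-level deviation has SD σ, the mean deviation among adherent visits is −bσ² × E[p(1−p)] / E[p]. With b = 0.12, σ = 7, E[p(1−p)] = 0.152 and E[p] = 0.753, this is −0.12 × 49 × 0.152 / 0.753 = −1.19, in line with the simulation. Weaker links give about −0.60 (b = 0.06; 0.156/0.770) and −0.30 (b = 0.03; 0.157/0.774).

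**6. Does the planned IV repair it?** No. Its instrument is measured household water salinity. That depends on randomised access, but also on whether the household chose to fetch and store MAR water, which is the same post-randomisation behaviour.

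**The case against.** The strongest reply has four parts.

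- **Own controls.** Every community crosses over, so adherers can be identified in every sequence. If adherence is a stable household trait, crossover timing remains random among adherers, and household and participant random effects absorb their level differences. This stands: steps 3 and 4 show no material bias in that case.
- **The sequence argument needs an unstated rule.** A reader might infer that first-sequence households must adhere at four visits and last-sequence households at one, so the estimate is biased. The article states no all-visits rule, use is recorded visit by visit, and unequal retention alone produced no bias. Both halves of that inference go too far.
- **Other behaviour change.** A reader might also infer that promoter-driven changes at access, such as less table salt, would be credited to the water only in this subgroup. The article has promoters delivering health messages from the start of the study, and Table 2 lists salt use as a covariate. Any change that access did trigger would also enter an estimate using access as instrument. If the 60% who adhere each fall by 1 mm Hg, the intention-to-treat effect shifts by 0.6, and 0.6/0.6 = 1.0. If everyone falls by 1 mm Hg, the shift is 1/0.6 = 1.67.
- **Low stakes.** Intention-to-treat is primary, and the Discussion assigns dilution to the IV analysis, not to this subgroup. This limits the importance of the point. It does not supply the missing caveat, and that IV analysis has the weakness shown in step 6.

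What the reply leaves untouched is time-varying adherence. The Discussion expects MAR salinity to vary by site and to change as the dry season intensifies. Households might drop exclusive use when the water becomes saltier, or tighten it after a high reading at a monthly visit. Both are inferences from the design; the article does not say that they will happen.

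**Conclusion.** The point holds as a risk, not as a demonstrated bias. The adherer subgroup conditions on post-randomisation behaviour in an unblinded trial, so randomisation does not protect its estimate, and the planned IV analysis does not restore that protection.

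Material bias needs adherence to move with time-varying blood pressure or its determinants. Under assumed links of increasing strength the size is roughly 0.3 to 1.3 mm Hg against the 3 mm Hg design effect. The direction could reverse if high readings prompt stricter use. With stable differences and household effects in the model, bias is small. Unequal selection by sequence arises only under an all-visits definition and in itself did no harm in the simulation. All adherence rates and variance parameters are assumptions, since the documents give none.

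The primary intention-to-treat analysis is unaffected.

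**What to change.** Make the main analysis of effect in users a complier-type IV analysis that keeps all participants:

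- **Instrument:** scheduled randomised access at each visit.
- **Exposure:** MAR water use at that visit, as any use or a graded measure (none, intermittent, exclusive).
- **Model:** visit effects and community-level clustering.
- **Sensitivity analysis only:** exclusive use as the exposure. Intermittent users may also benefit from access, which violates the exclusion restriction. Their benefit would be credited to exclusive users, inflating the estimate by (share intermittent / share exclusive) × effect in intermittent users.

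No access before handover makes non-compliance one-sided, which suits this estimator. Keep the adherer subgroup only as exploratory, with adherence defined in advance and a statement that randomisation does not protect it.

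**Cost:** a change of wording and one further model on data already being collected. The interval will be wider than the subgroup's. The estimate will still include any other behaviour change triggered by access and will still rely partly on reported use, although the stored-water measurements allow a cross-check. The graded version also assumes a shape for the dose-response.

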### Objectives

Randomised controlled trials demonstrate that reduction in dietary sodium in adults decreases blood pressure among people both with and without hypertension.^47–49^ Meta-analysis of randomised trials also suggests modest reduction in salt intake for 4 or more weeks causes significant reduction in blood pressure at the population level.^50 51^ The primary objective of the study is to assess whether access to low-salinity MAR water can reduce blood pressure of community members ≥20 years of age. Secondary objectives include whether access to MAR water can reduce urinary sodium and total protein excretion. We will evaluate water salinity, urinary sodium excretion and blood pressure so that we understand whether or not we achieved our immediate targets along the causal pathway.

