### Sample size

The sample size of the stepped-wedge trial was calculated based on the effect of MAR systems to reduce systolic blood pressure of the ≥20-year-old community members. Data from southwest coastal Bangladesh demonstrated a 7 mm Hg lower mean systolic blood pressure among pregnant women who drank pond water compared with those who drank brackish water, and a 17 mm Hg lower mean systolic blood pressure for pregnant women who drank rainwater compared with those who drank brackish water.^35^ The mean reduction in systolic blood pressure following long-term modest salt reduction is 4.2 mm Hg.^50^ For calculations, we considered a mean systolic blood pressure reduction of at least 3 mm Hg among the communities who will have access to MAR water for drinking and cooking purposes compared with those who will use brackish water. The entire population under the MAR community catchment area will be considered as one cluster. Each MAR community serves approximately 300 people, constituting 60–70 households in the catchment area.^28^ The mean household size in southwest coastal Bangladesh is 4.2, approximately 52% of household members are ≥20 years old.^58 59^ Since we will collect blood pressure from all household members ≥20 years old, we estimated an average of 2.2 participants in this age group per household. We will select 28 households per cluster (28×2.2=60 people per cluster). A previously published study in Bangladesh reported SD 13.51 for systolic blood pressure,^60^ but we considered SD 20 for systolic blood pressure to capture a greater variation of blood pressure. We calculated the sample size for the stepped-wedge trial adopting the formula used by Hussey and Hughes.^61^ Although their formula assumed no within-participant correlation over time (cross-sectional design), we applied their formula for a cohort design (same participant followed up over time). The salinity problem and the MAR water quality may be influenced by seasonality over the progression of dry season and participants’ blood pressure may respond differently to different level of sodium exposure in MAR drinking water. Therefore, it is important that we investigate the effect of the MAR system on the same participants over the entire dry season. Since we will investigate the same participants in each step, we will have less participant-level variability and sufficient power compared with a cross-sectional design to investigate the effect of MAR systems. We initially calculated the sample size for a simple unadjusted trial (N_U_), and then multiplied by the design effect for a stepped-wedge trial (DE_SW_). The sample size for a simple unadjusted trial was calculated as 1396 participants (effect size=3, SD of 20 for both groups, 80% power and 5% type I error). The DE_SW_ was 3.04 based on a formula provided by Hussy and Hughes, therefore sample size was 1396×3.04. We also inflated the total sample size considering 10% loss to follow-up. We then followed the approaches of determining the number of clusters required for total sample size considering a fixed cluster size of 60.^62^ We then calculated the number of steps that we need to randomise by dividing the total cluster by steps. We calculated that 16 MAR communities will be required for the study with four communities randomised to access MAR water in each step (figure 3).

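### The time-since-access analysis depends on a positive result, although the single access effect in this wedge is close to a first-visit effect and could miss a delayed one

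*Protocol article*

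**What the plan says.** All references are to the protocol article.

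- **Statistical methods.** The primary analysis is an intention-to-treat mixed model for systolic blood pressure, with random effects for community, household and participant and fixed effects for visit. The exposure of interest is access to MAR water. Neither this section nor its Table 2 names a time-since-access term. Time to effect is a secondary analysis with a condition attached: "If the trial demonstrates drinking MAR water has health effects, we will investigate the time required for health effects following receiving MAR intervention".
- **Study design.** There are five monthly steps, the first a baseline. "During each subsequent month, four randomly selected communities will receive access to MAR water for drinking and cooking".
- **Objectives.** The rationale includes evidence that "modest reduction in salt intake for 4 or more weeks causes significant reduction in blood pressure at the population level".
- **Sample size.** The plan cites a long-term figure, "The mean reduction in systolic blood pressure following long-term modest salt reduction is 4.2 mm Hg", and then sets its own target: "we considered a mean systolic blood pressure reduction of at least 3 mm Hg among the communities". That target is a single difference, used with the Hussey and Hughes formula.
- **Data collection methods.** Successive visits are at least 4 weeks apart.
- **Other secondary analyses.** The adherent-household subgroup (Statistical methods) and the salinity-level and instrumental-variable analyses (Discussion) carry no such condition, but none of them models lag.

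**The concern.** The plan treats the timing of the effect as an open question, since it intends to study it. It does so only once an effect has been shown. That order is safe if the primary estimate is a fair average over exposure time. With visit fixed effects in a stepped wedge it is not: by the later visits most communities are exposed, so long-exposed communities serve as comparators for newly exposed ones, and any extra benefit they have gained is subtracted.

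The introduction says the trial is meant to inform decisions on scaling up MAR. A null that really means no effect yet at the first post-handover visit would mislead that decision. A lag analysis added after a null would be post hoc and carry little weight.

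**Working it through.** **1. Reproduce the plan's figures.** The inputs are from Sample size: difference 3 mm Hg, "we considered SD 20 for systolic blood pressure to capture a greater variation of blood pressure", and "80% power and 5% type I error".

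- N = 2 × 2 × (1.96 + 0.8416)² × 20² / 3² = 1395.4, or 698 per arm and 1396 in total. This matches "The sample size for a simple unadjusted trial was calculated as 1396 participants".
- The stepped-wedge design effect with 4 steps, one measurement per step and 60 per community is 0.609 × 5 visits = 3.046 at ICC 0.05 (3.03 to 3.05 for ICC 0.04 to 0.06). The plan states 3.04. It does not state an ICC; 0.05 is inferred from this match.
- 1396 × 3.04 = 4244 observations; / 0.9 = 4715; / (60 × 5) = 15.7, hence 16 communities.

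**2. Exposed community-visits.** By months since handover there are 16, 12, 8 and 4, or 40 in all. The first post-handover visit supplies 16/40 = 40%.

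**3. What the single coefficient estimates.** The purely within-community limit can be checked by hand. Let X = 1 when sequence i (1 to 4) is exposed at visit j (0 to 4). Subtract the row mean (5 − i)/5 and the column mean j/4, and add the grand mean 0.5. The residuals in the exposed cells are:

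| Sequence | Month 1 | Month 2 | Month 3 | Month 4 |
|---|---|---|---|---|
| 1 | 0.45 | 0.20 | −0.05 | −0.30 |
| 2 | 0.40 | 0.15 | −0.10 | |
| 3 | 0.35 | 0.10 | | |
| 4 | 0.30 | | | |
| Sum | 1.50 | 0.45 | −0.15 | −0.30 |

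Dividing by the total of 1.50 gives weights +1.00, +0.30, −0.10, −0.20. Generalised least squares with a community random effect (60 per community, no within-person correlation) gives:

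- ICC 0.05: +0.962, +0.300, −0.081, −0.181.
- ICC 0.01: +0.86, +0.30, −0.03, −0.13.

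Across ICC 0.01 to 0.5 the month-1 weight is about 0.85 to 1.00, and months 3 and 4 are always negative. Adding household and participant correlation moves the weights towards the within-community limit.

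**4. Expected estimates at ICC 0.05** (effects in mm Hg at months 1 to 4):

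- Linear rise 0.75, 1.5, 2.25, 3: 0.962×0.75 + 0.300×1.5 − 0.081×2.25 − 0.181×3 = **0.45**; true average 1.88.
- One-visit lag 0, 3, 3, 3: 3 × (0.300 − 0.081 − 0.181) = **0.11**; average 2.25.
- Half, then full (1.5, 3, 3, 3): 0.962×1.5 + 0.11 = **1.56**; average 2.63, ratio about 60%.
- Fast rise, 63/86/95/98% of 3: **1.83**; average 2.57, ratio 71%.

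**5. Power.** The SE of the single coefficient is 1.01 at 60 per community and 1.06 at 54 (60 × 0.9), both at ICC 0.05 with no within-person correlation. With assumed participant shares of variance up to 0.65 it falls to about 0.53.

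- Linear rise: about 7 to 11% over these assumptions.
- One-visit lag: about 5 to 7%, essentially the type I error.
- Half, then full: 31% at 54 and 34% at 60 per community (ICC 0.05, no within-person correlation), and more with within-person correlation.

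**6. Months-since-handover model.** With four indicators, the average over months is unbiased for any of these shapes. At 60 per community and ICC 0.05 the SEs by month are 1.09, 1.44, 1.90 and 2.58, and 1.55 for the average. At 54 the SE of the average is 1.62 against 1.06 for the single effect, so power for a constant 3 mm Hg is about 46% against 81%.

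**The case against.** **The effect may be largely present by the first visit.** The Objectives expect a response to salt reduction lasting 4 weeks or more, and visits are at least 4 weeks apart. If handover closely follows a visit, the first post-handover measurement falls about when an effect is expected. The text does not fix that gap, and Figure 3 is not shown. This stands: a reader might infer that the documents imply a slow build-up over four months, but no section says so. They make a lag plausible, no more.

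**Near zero is not the general result.** A reader might infer that any gradual effect vanishes. Step 4 shows otherwise: with half or more of the effect present at the first visit, the estimate is attenuated but survives. This stands.

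**The single-effect model is consistent with the sample-size method and is more precise.** This also stands. Replacing it would trade bias for variance, at the power cost in step 6. For the fast rise, the averaged model has slightly less power than the planned one (0.35 against 0.41 at 54 per community).

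**The wording does not forbid a lag analysis after a null result, and an unseen analysis plan may code exposure differently.** Both are fair: a single constant effect is the natural reading of the model, not a stated one. The condition on the time-to-effect analysis, however, is in the published text. A promise made only for a positive result leaves nothing pre-specified for a null.

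**Conclusion.** The point holds in a limited form and should be fixed. The only time-since-access analysis is tied to a positive result, while the primary coefficient, as described, mostly reflects the first post-handover visit and gives negative weight to the longest exposures. That weight pattern follows from the layout and is stable across ICC 0.01 to 0.5.

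The size of the bias depends on the shape of the effect, which the documents do not give. It is severe for a roughly linear build-up or a one-visit lag and moderate when half or more of the effect is there at the first visit. It is absent for an immediate constant effect. The power figures rest on an ICC and a within-person correlation that the plan does not state.

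The documents do not support the stronger conclusions that the primary model is wrong or that the trial will miss a real effect.

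**What to change.** 1. Delete the condition in Statistical methods, so that time to effect is studied whatever the primary result.
2. Pre-specify, as a secondary analysis, the primary model with the access term replaced by indicators for 1, 2, 3 and 4 months since handover. Report the four effects and their average with confidence intervals beside the primary estimate.
3. State that a null single-effect estimate will not be read as no effect without that analysis.
4. Keep the single-effect model as primary.

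The cost is wording and analysis code, because handover follows the randomisation schedule. No further data are needed and the power of the primary test is unchanged. The secondary estimates will be imprecise, especially at month 4, and should be presented as such.

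A lighter alternative, one indicator for the first post-handover visit plus one later term, does not remove the problem. At ICC 0.05 the later term weights months 2 to 4 at about +1.04, +0.15 and −0.19. Under the linear rise that gives 1.04×1.5 + 0.15×2.25 − 0.19×3 = 1.3 against a true average of 2.25 for those months.
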